**Session 1: Program orientation, relationship building, and needs assessment (~75 minutes)**
The navigator will build rapport by introducing themselves, their role, and the program. The navigator will identify significant contacts, and complete study documentation (eg, release of information forms). Finally, the navigator will conduct a comprehensive needs assessment of sexual health and substance use to develop an individual risk reduction plan. Relevant community resources will be presented to the participant.eHealth approaches identified in aim 1 (eg, SMS text messages, appointment reminders, motivational messages, and telehealth sessions) will be incorporated into session content.
**Session 2: Substance use education and treatment cascade (~60 minutes)**
Provide psychosocial education on substance use (tailored to the client’s behaviors and needs identified in session 1), provide participants with information on how patterns of substance use can affect their health, social, and legal outcomes and the Juvenile Justice Behavioral Health Services Cascade. The navigator will revisit the risk reduction plan (session l) and tailor it to any changes in the participant's life. Participants will be referred to local substance use treatment.eHealth approaches identified in aim 1 (eg, SMS text messages, appointment reminders, motivational messages, and telehealth sessions) will be incorporated into session content.
**Session 3: HIV and Pre-exposure Prophylaxis knowledge and care cascade (~60 minutes)**
Provide psychosocial education on sexual health (tailored to the client’s behaviors and needs identified in session 1) and can shape an individual’s risk of sexually transmitted infections and HIV. Provide basic HIV (eg, transmission) and pre-exposure prophylaxis information, and outline the pre-exposure prophylaxis Care Continuum. The navigator will revisit the risk reduction plan (session 1) and tailor to any changes in the participant’s life. Participants will be referred to local pre-exposure prophylaxis–related services.eHealth approaches identified in aim 1 (eg, SMS text messages, appointment reminders, motivational messages, and telehealth sessions) will be incorporated into session content.
**Session 4. Substance use and Pre-exposure Prophylaxis care appointment scheduling and goal setting (~60 minutes)**
Provide follow-up information on where and how to access substance use and pre-exposure prophylaxis–related services. Develop a plan for substance use and pre-exposure prophylaxis linkage and maintenance to include planning for transportation to health care services, keeping appointment dates, obtaining medication (pre-exposure prophylaxis), formulating a medication schedule, and identifying motivation for appointment attendance and pre-exposure prophylaxis adherence.eHealth approaches identified in aim 1 (eg, SMS text messages, appointment reminders, motivational messages, and telehealth sessions) will be incorporated into session content.
**Follow-up contacts (~30 minutes)**
Maintain regular contact between the navigator and the participant, provide guidance and support for goal setting, and ongoing emotional and psychosocial support.eHealth approaches identified in aim 1 (eg, SMS text messages and telehealth) will be incorporated to support follow-up contacts.

#### Navigator Training

The Navigator will receive a minimum of 7 days of training focused on relational service provisions (ie, emotional and psychosocial support), logistical service provisions (ie, assistance to overcome task-oriented barriers like scheduling and finding transportation to appointments), technology training, and population-specific training (eg, carceral system processes and harms perpetuated by the carceral system) [51]. Aim 1 system partner interviews will inform additional areas of training relevant to implementing a peer-led model, as well as preferred navigator characteristics (ie, peer navigators will share an age range and at least 1 intersecting identity or experience such as CLI, PrEP use, or substance use treatment with participants).

#### Intervention Fidelity

During the open pilot, navigators will audio record and complete a checklist documenting the delivery of session material [52]. Navigators will engage in weekly supervision with the principal investigator, and the principal investigator will periodically audit records and conduct field visits to observe sessions (required activities will be rated for completeness using a 4-point scale ranging from 0 “not at all” to 3 “completely”).

#### Exit Interviews

The research team will collect qualitative feedback on the open pilot regarding intervention content, structure, and delivery (type of contact, ie, in-person or over the phone, eHealth [Chorus] enhancement acceptability, and a number of contacts) via individual interviews with CLI-YAs. We will also obtain feedback from system partners regarding intervention recruitment, referral, delivery, and implementation. The navigator will be actively involved in the intervention pilot testing as well as in making further intervention manual revisions according to their lived experience of navigation delivery. Exit interview data will be analyzed using rapid qualitative analysis methods to reduce the time completing analysis to ensure timely results for use in aim 3; rapid analysis has been shown to have considerable overlapping findings with traditional qualitative analytic approaches [53,54].

#### Open Pilot Outcomes

In addition to completing a 7-day minimum navigator training, the open pilot’s primary outcome is qualitative feedback to assess appropriateness and satisfaction. The results will be used to refine the intervention for pilot testing in aim 3.

### Aim 3: Pilot Randomized Controlled Trial Phase

#### Participants

To assess the feasibility, acceptability, and impact of the adapted eHealth-enhanced intervention for CLI-YAs, we will test the intervention in a randomized pilot trial with CLI-YAs (n=75).

#### Recruitment and Randomization

Recruitment procedures will be informed by aim 2 results. Participants will be randomized either to the intervention group (n=50) or the standard of care (n=25) using a 2:1 randomization allocation scheme (Figure 2). Figure 3 provides a schematic of our study processes. Each participant will complete a baseline assessment immediately following the consent process. At the end of the baseline assessment, participants will be randomized to the intervention or control condition using a computerized algorithm programmed into REDCap (Research Electronic Data Capture; Vanderbilt University). Randomization will be blocked to avoid “runs” of assignment to the same.

**Figure 2 figure2:**
[figure not shown]
Randomization protocol for aim 3, a 90-day randomized controlled trial designed to link young adults impacted by the criminal legal system to substance use and HIV prevention services in Allegheny County, PA. PrEP: pre-exposure prophylaxis.

#### Standard of Care

The standard of care is a referral to substance use treatment and HIV prevention services from an individual’s case worker.

#### Data Collection

The baseline assessment will occur immediately following participant consent, prior to randomization, and follow-up assessments will occur at 1 month and 3 months (Figure 3). Data will be collected via face-to-face one-on-one interviews in private locations to ensure confidentiality. If face-to-face interviews are not possible, a participant will be given the option of completing the assessment via a secure web-based survey link. Regardless of the method of interview administration, REDCap will be used to collect data (ie, in person on tablets or via a secure REDCap survey sent via email). If completing the assessment via a secure link, specific instructions will be provided to the participant to inform them about how to keep their data private.

**Figure 3 figure3:**
[figure not shown]
Recruitment, randomization, and intervention practices for aim 3, a 90-day randomized controlled trial designed to link young adults impacted by the criminal legal system to substance use and HIV prevention services in Allegheny County, PA. PrEP: pre-exposure prophylaxis.

#### Pilot Trial Outcomes

Primary outcomes are linkage to substance use treatment and PrEP services. Because PrEP and substance use treatment health service linkage are a process and not a 1-time event, we will also explore prelinkage (eg, navigator satisfaction) and downstream outcomes (eg, PrEP initiation, adherence, and substance use treatment continuing of care) in an exploratory fashion [55]. The navigator will track these outcomes, but the primary outcomes of (1) PrEP linkage will be attendance at a PrEP services appointment, verified by medical records and (2) substance use treatment linkage will be attendance at a substance use treatment appointment, verified by the navigator and medical provider collateral (if the participant agrees). Other exploratory outcomes include time to health service linkage (substance use and PrEP) and data on HIV testing at the PrEP linkage appointment (uptake, result). Participants will be asked whether and for how long they have experienced hospitalization, residential treatment, and detention since the intervention to account for any system barriers to linkage. We will also assess preferred methods for communicating with the navigator as well as participant satisfaction with the intervention and navigator services. Table 1 provides additional detail on outcomes and correlates.

**Table 1 table1:** Description and schedule of outcomes from a 90-day randomized controlled trial designed to link young adults impacted by the criminal legal system to substance use and HIV prevention services in Allegheny County, PA.

Primary outcomes		Baseline		30 days		90 days
PrEP^a^ linkage: medical record				✓		✓
Substance use treatment linkage: self-report, medical provider collateral if the participant agrees				✓		✓

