### Aim 1: Development Phase

#### Participants

We present eligibility criteria by separate participant population. CLI-YAs (ages 18-29 years; n=24) will be eligible if they self-report recent CLI (past year); self-identify as HIV negative; endorse behaviors in the past 6 months indicating consideration of PrEP per the Center for Disease Control and Prevention’s risk indices [44]; meet the Tobacco, Alcohol, Prescription medication, and other Substance use Tools’ criteria for identifying the Diagnostic and Statistical Manual of Mental Disorders SUD (ie, ≥2 for tobacco, alcohol, and marijuana, and ≥1 for other substances) [45]; and are conversant in English. Exclusion criteria include being on PrEP, cognitive delays that would interfere with consent or participation, or inability to provide contact information for ≥2 locator individuals. CL system partners (n=2) will be in probation administration or frontline staff (eg, probation officers). Medical or public health system partners (n=2) will be involved in substance use treatment delivery and PrEP participant care in a setting where CLI participants are referred and will include individuals who have had experience navigating CLI to health services.

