### Aim 2: Open Pilot Phase

#### Participants

To refine and test the adapted eHealth-enhanced intervention for CLI-YA, we will pilot the intervention with CLI-YAs (n=10). Final eligibility criteria for aims 2 and 3 will be determined from insights gained through the implementation and data collection of aim 1.

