#### Aim 2: Pilot Trial Phase

Prior to participation in the pilot trial, CLI-YAs will undergo a 2-step consent process. Potential participants will be given an information sheet and provide verbal informed consent for screening. Next, should individuals be interested in participating and eligible based on their HIV risk assessment and SUD screening, they will provide written informed consent to allow participation in the open pilot navigation intervention and exit interview. Participants will be compensated US $40 for participating in exit interviews.

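### Aim 3 counts any attended substance use treatment visit as linkage, so routine visits in ongoing treatment would score as success in both arms unless the outcome is limited to new treatment

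*Protocol article*

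**What the plan says.** - **Outcome.** Pilot Trial Outcomes (Aim 3) names two primary outcomes, PrEP linkage and substance use treatment linkage. For the second: "substance use treatment linkage will be attendance at a substance use treatment appointment". Nothing requires a first visit, a new provider or a new episode. Table 1 schedules the outcome at 30 and 90 days only.
- **Coding and analysis.** Data Management and Analysis (Aim 3) turns the month 1 and month 3 assessments into one yes/no indicator of whether linkage ever happened, and relates it to condition by logistic regression. No restriction to, or adjustment for, people untreated at baseline is stated. Substance use treatment behaviours appear only among the exploratory moderators.
- **Eligibility.** The only exclusion list is under Aim 1, for the focus groups: "Exclusion criteria include being on PrEP, cognitive delays that would interfere with consent or participation, or inability to provide contact information for ≥2 locator individuals". Current substance use treatment is not on it. For the later aims, the Participants section of Aim 2 says: "Final eligibility criteria for aims 2 and 3 will be determined from insights gained through the implementation and data collection of aim 1".
- **Size.** Participants are "randomized either to the intervention group (n=50) or the standard of care (n=25) using a 2:1 randomization allocation scheme".
- **Baseline data.** Table 1 lists Health care use at baseline and 90 days, without describing its content.

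**The concern.** The intervention is meant to refer and link people to treatment. Someone already in treatment when randomised needs no linking, yet under the stated rule the next routine visit scores as linkage.

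It is plausible that such people will enrol. The Aim 1 criteria select for a positive substance use disorder screen, and Aim 2 recruitment takes place in probation offices and community organisations. The standard of care is itself a case-worker referral to treatment, so some people may have been referred before enrolment.

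Their visits would raise the linkage rate in both arms and shrink the contrast. The exploratory time-to-linkage outcome would be affected too, because it would record the wait to a routine visit. The article says the results will feed a future multilevel trial, so an inflated control rate and a diluted effect could carry over into its planning.

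**Working it through.** **Inputs from the article:** 50 intervention and 25 control participants (75 at 2:1, which agrees). It gives no linkage rates, effect size, power or share already in treatment, so there is no figure of its own to reproduce.

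**Assumptions:** among people not in treatment at baseline, linkage is p0 = 20% (control) and p1 = 45% (intervention). A share π is already in treatment, and all of these people are scored as linked in either arm. The test is two-sided at 5%.

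**Observed rates.** In each arm q = π + (1 − π)p, so q1 − q0 = (1 − π)(p1 − p0). The difference shrinks by exactly the share π.

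**Power** (normal approximation), with q̄ = (50·q1 + 25·q0)/75:

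z = [(q1 − q0) − 1.96·√(q̄(1 − q̄)(1/50 + 1/25))] / √(q1(1 − q1)/50 + q0(1 − q0)/25), and power = Φ(z).

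Worked case, π = 20%:
- q0 = 0.20 + 0.80 × 0.20 = 0.36; q1 = 0.20 + 0.80 × 0.45 = 0.56; difference 0.20.
- q̄ = (50 × 0.56 + 25 × 0.36)/75 = 0.493. The null standard error is 0.1225 and the alternative standard error 0.1189.
- z = (0.20 − 1.96 × 0.1225)/0.1189 = −0.34, so power = 0.37.

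| π | Control | Intervention | Difference (points) | OR | Power, all 75 | Power, untreated at baseline only |
|---|---|---|---|---|---|---|
| 0% | 20% | 45% | 25 | 3.27 | 0.57 | 0.57 |
| 20% | 36% | 56% | 20 | 2.26 | 0.37 | 0.47 |
| 40% | 52% | 67% | 15 | 1.87 | 0.25 | 0.36 |

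The last column applies the same formula to p0 and p1 with arms of 50(1 − π) and 25(1 − π). The smaller sample does better because the difference stays at 25 points.

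**Other assumed rates, at π = 30%:**

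| Control vs intervention | Power at π = 0 | All 75 | Untreated only |
|---|---|---|---|
| 20% vs 50% | 0.73 | 0.41 | 0.56 |
| 15% vs 40% | 0.61 | 0.30 | 0.44 |
| 10% vs 30% | 0.49 | 0.20 | 0.34 |

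**Chance imbalance.** The SD of the between-arm difference in the share already in treatment is √(π(1 − π)(1/50 + 1/25)): 7 points at π = 10%, 10 at 20%, 11 at 30% and 12 at 40%. As an example with p0 = 20% and p1 = 45%, let the share be 20% in the intervention arm, where q1 = 0.56.
- Control share 30%: q0 = 0.30 + 0.70 × 0.20 = 0.44, difference 12 points.
- Control share 10%: q0 = 0.10 + 0.90 × 0.20 = 0.28, difference 28 points.

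An imbalance of about one SD therefore moves the estimate by about 8 points either way around 20. The binomial variance of q already contains this, so it is not a further deduction from the power figures above.

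**The case against.** **Eligibility is open.** A reader might infer that people already in treatment are admitted to the trial. The article does not say so: the exclusion list governs the focus groups, and the Aim 3 criteria are deferred. For the same reason one cannot say that the trial protects the PrEP outcome from prevalent users but not the substance use outcome; neither exclusion is fixed for Aim 3. The consent text, which has people "eligible based on their HIV risk assessment and SUD screening", does not settle it either, since it also leaves out age and PrEP use. This part of the objection stands.

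**Linkage is framed as an early step.** The Pilot Intervention Navigation Protocol takes people from screening to linkage and places continuing care downstream, and Pilot Trial Outcomes does the same. That shows what linkage is meant to be, but the scoring rule does not enforce it.

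**Baseline data may exist.** Health care use may already capture current treatment, so that part of the remedy may be in place. The stated primary analysis still does not use it.

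**The size is hypothetical and near an upper bound.** Every rate is assumed, and the model scores all people in treatment as linked. Navigators also help with transport and keeping appointments. If that raised attendance among people already in treatment from r0 to r1, the difference would be (1 − π)(p1 − p0) + π(r1 − r0), a smaller dilution. The article sets no power target for this pilot, so lost power alone is not decisive. These limits stand.

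**Exclusion is debatable.** The Aim 1 screen covers tobacco, alcohol, marijuana and other substances. A person treated for one may need linkage for another, so a blanket exclusion could remove intended beneficiaries. This also stands, and it shapes the fix.

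**Conclusion.** The point holds for the outcome definition and its coding, both of which the article states for Aim 3. Unless the final criteria or the definition address it, ongoing treatment would be scored as linkage in both arms. The risk difference would shrink by about the prevalent share: from 25 to 20 points at an assumed 20% and to 15 points at an assumed 40%, given assumed linkage of 20% versus 45%. The actual share is unknown; if few participants are in treatment, the effect is small.

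A reader might also infer bias in favour of one arm. The documents do not support that: randomisation balances prevalent treatment in expectation. What remains is dilution, and chance imbalance with a control arm of 25. The change should be made, and it is easiest now, while the Aim 3 criteria are still to be set.

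**What to change.** 1. Record current substance use treatment, by substance, at the baseline assessment, which precedes randomisation. First check whether the Health care use measure already captures it.
2. Define linkage as the first attended visit of a new treatment episode after randomisation, and state what makes an episode new, including the case of a person treated for one substance who starts treatment for another. Use the same definition for time to linkage.
3. Analyse this outcome in participants not in treatment at baseline. Because status is fixed before randomisation, the comparison remains a randomised one. Report people already in treatment separately.

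Excluding people in current treatment when the Aim 3 criteria are set is an option for the sponsor, not a requirement.

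Cost: at most one baseline question, one or two sentences in the outcome definition, and a smaller denominator for this outcome only (60 instead of 75 at a 20% share, since 0.80 × 75 = 60). PrEP linkage keeps all 75.

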**Secondary outcomes**						
	Navigator satisfaction: NAVSAT Pt 1		✓			
	Client intervention satisfaction: Study Participant Feedback Questionnaire	✓	✓		✓	
	PrEP care continuum (accepted, initiated, and adhered): navigator report, medical record, and self-report		✓		✓	
	Substance use treatment continuum (accepted, initiated, and adhered): navigator report, medical record, and self-report		✓		✓	
	Linkage to other services: self-report and Navigator report		✓		✓	

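### Substance use linkage, a primary outcome, has two incompatible sources, and the one in the text relies on a navigator whom the control arm is not described as having

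*Protocol article*

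**What the plan says.** The aim 3 pilot is "randomized either to the intervention group (n=50) or the standard of care (n=25) using a 2:1 randomization allocation scheme". Its two primary outcomes are linkage to PrEP services and linkage to substance use treatment.

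- **Substance use linkage, text of Pilot Trial Outcomes:** "attendance at a substance use treatment appointment, verified by the navigator and medical provider collateral (if the participant agrees".
- **Substance use linkage, Table 1, primary outcomes:** "Substance use treatment linkage: self-report, medical provider collateral if the participant agrees". The navigator is not named here.
- **PrEP linkage, same text:** "attendance at a PrEP services appointment, verified by medical records". Table 1 also names the medical record.
- **Control arm, Standard of Care:** "The standard of care is a referral to substance use treatment and HIV prevention services", made by the participant's case worker. No navigator is mentioned.
- **Table 1, secondary outcomes:** navigator report is named where it is meant, for example "Linkage to other services: self-report and Navigator report".
- **Textbox 1, Session 1:** the navigator's tasks include to "complete study documentation (eg, release of information forms".

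Under Data Management and Analysis, the primary analysis is a logistic regression of linkage on condition. The dependent variable is dichotomous and records whether linkage ever occurred, using the month 1 and month 3 assessments.

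**The concern.** The text and Table 1 share provider collateral but differ on the other source. The text has the navigator and no self-report; the table has self-report and no navigator. Table 1 does name navigator report in its secondary rows, so its absence from the primary row is unlikely to be shorthand.

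The choice matters because the navigator belongs to the tested intervention. Collateral depends on the participant's agreement. Under the text, an intervention participant who declines collateral still has a navigator who can confirm attendance. A control who declines has no named verifier. The navigator also knows the allocation and would be confirming the result of his or her own work.

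What is at stake is the between-arm comparison on a primary outcome. If control attendances are missed more often than intervention attendances, the trial can show a difference where navigation has no effect.

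**Working it through.** The article states no expected linkage rate, effect size, power or detection rate, so there is no figure of the plan's own to reproduce. The 2:1 split is arithmetically right: 75 × 2/3 = 50 and 75 × 1/3 = 25.

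**Step 1. Can each rule be applied in each arm?**

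| Source | Intervention | Control |
|---|---|---|
| Navigator (text only) | available | none described |
| Self-report (Table 1 only) | available | available |
| Provider collateral (both) | if participant agrees | if participant agrees |

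Only the Table 1 rule uses sources that exist in both arms.

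**Step 2. Size under no true effect (illustration).** All rates here are assumptions. With no false positives, observed rate = true rate × detection. Take 40% true linkage in both arms and 95% detection in the intervention arm.

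- Intervention: 0.40 × 0.95 = 0.38, that is 19 of 50.
- Control at 80% detection: 0.40 × 0.80 = 0.32 (8 of 25). Difference 6 points; odds ratio (0.38/0.62)/(0.32/0.68) = 1.30.
- Control at 70%: 0.28 (7 of 25). Difference 10 points; odds ratio 1.58.
- Control at 60%: 0.24 (6 of 25). Difference 14 points; odds ratio 1.94.

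True linkage of 40% means 10 linked controls, so these cases amount to missing 2, 3 or 4 people.

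**Step 3. Effect on a test.** This uses exact binomial enumeration of a two-sided pooled z test, with 50 against 25 participants, an assumed 5% level and 30% true linkage in both arms.

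| Control detection (intervention 95%) | Observed rates | Odds ratio | Chance of a false result favouring the intervention |
|---|---|---|---|
| 85% | 28.5% vs 25.5% | 1.16 | 4.1% |
| 70% | 28.5% vs 21.0% | 1.50 | 9.4% |
| 50% | 28.5% vs 15.0% | 2.26 | 24.3% |

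With 95% detection in both arms, the odds ratio is 1.00 and this chance is 2.3% to 3.0% for true rates of 20% to 50%.

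**Step 4. Can the direction reverse?** Suppose the intervention arm is verified with no false positives, while control self-reports are accepted unverified with 95% sensitivity and 10% false positives. At 30% true linkage, control shows 0.30 × 0.95 + 0.70 × 0.10 = 0.355 against 0.285 in the intervention arm. The odds ratio is (0.285/0.715)/(0.355/0.645) = 0.72, against the intervention. The direction therefore depends on which rule staff follow.

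**The case against.** The strongest reply is that Table 1 is the operative definition. The text refers to it for further detail on outcomes. The analysis section builds the dependent variable from the month 1 and month 3 assessments, which Data Collection describes without distinguishing the arms. Under Table 1 the named sources are the same for everyone. This has force: it rules out saying that the arms *are* ascertained unequally. It does not remove the conflict, because the sentence that defines the primary outcome still names the navigator.

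Three stronger readings are tempting, and the document does not support them:

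- **That the effect is certainly biased toward the intervention.** That direction is likely if the text is followed, but Step 4 shows that it can reverse. The article also does not say how an attendance that nobody verified would be coded.
- **That releases would come mainly from engaged intervention participants, which would compromise PrEP records too.** The release forms appear as an example within sample session content introduced under the aim 2 open pilot. Nothing says that these are the only releases, or that they serve outcome verification. PrEP linkage has the same source in text and table.
- **That this effect estimate will be carried into the next trial.** The article says only that results will contribute to developing and testing it.

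Two further limits stand. That controls have no navigator is inferred from the described arms, and Figures 2 and 3 are not shown. The secondary outcomes that use navigator report are exploratory, and both continuum rows also list medical record and self-report.

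**Conclusion.** The point holds for substance use treatment linkage only. The article gives two incompatible sources for this primary outcome. The one in the text cannot be applied equally in both arms as they are described, and it makes the unblinded interventionist a verifier. If the text is followed, bias toward the intervention is likely. Its size cannot be derived from the article; the 6 to 14 points in the illustration rest entirely on the assumed 40% true linkage and on detection of 95% against 60% to 80%. If Table 1 is followed, the risk is smaller and depends on whether self-report and agreement to collateral differ between arms. The conflict should be resolved before aim 3 data collection, because unequal ascertainment cannot be fully repaired afterwards.

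**What to change.** 1. Make the text of Pilot Trial Outcomes agree with Table 1: self-report at 30 and 90 days plus provider collateral where the participant agrees.
2. State that this one rule applies identically in both arms, including what counts when collateral is refused.
3. Remove the navigator as verifier of the primary outcome. Keep navigator report to describe process.
4. Seek release-of-information permission from all 75 participants at the aim 3 baseline assessment, which already precedes randomisation, so that access to collateral does not depend on arm.

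The cost is protocol wording, a few minutes at baseline, and possibly a slightly lower observed linkage rate in the intervention arm.

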#### Exit Interviews

We will conduct exit interviews with a subsample of intervention arm participants (n=10), the navigator (n=1), and partners from participating systems (n=4). Interviews will assess intervention acceptability and suggestions for improvement. To recruit for qualitative exit interviews, a member of the study team will contact intervention participants to invite them to a phone interview (~30 minutes). To ensure a range of responses, we will sample for (1) participants who connect or did not connect to the navigator and who linked or did not link to PrEP and substance use treatment services and (2) variation in characteristics that may impact the intervention (eg, psychiatric symptoms). We will seek to understand reasons why the intervention was or was not successful for a particular participant (via participant and navigator report). To analyze exit interview data, we will mirror aim 2’s rapid qualitative analysis processes.

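### The article gives two incompatible source rules for the substance use treatment primary outcome, and the one in the text cannot be applied equally to both arms

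*Protocol article*

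**What the plan says.** Aim 3 has two primary outcomes, linkage to PrEP services and linkage to substance use treatment. Pilot Trial Outcomes states the source for each twice, once in the running text and once in Table 1.

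- **PrEP linkage.** The text has "attendance at a PrEP services appointment, verified by medical records", and Table 1 also names the medical record. The two agree.
- **Substance use treatment linkage.** In the text, attendance is "verified by the navigator and medical provider collateral (if the participant agrees". Table 1 has "Substance use treatment linkage: self-report, medical provider collateral if the participant agrees".

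The text adds: "The navigator will track these outcomes".

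On the arms, Recruitment and Randomization states: "Participants will be randomized either to the intervention group (n=50) or the standard of care (n=25) using a 2:1 randomization allocation scheme". The control condition is described in one sentence: "The standard of care is a referral to substance use treatment and HIV prevention services from an individual’s case worker". The aim 3 Exit Interviews section counts "the navigator (n=1"), which points to one navigator.

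Under Data Management and Analysis, the primary analysis is a logistic regression of an ever-linked indicator, taken over the month 1 and month 3 assessments, on condition.

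**The concern.** The two statements are different rules for one primary outcome. A participant who reports attending, but whom neither the navigator nor a provider confirms, is linked under Table 1 and not linked under the text. The article does not say which rule governs.

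The text rule also raises a question of comparability. Navigation is the experimental treatment, and nothing describes a navigator for controls. Under the text, a control who does not agree to provider collateral has none of the verifying sources named for this outcome, while an intervention participant who does not agree still has the navigator. That navigator delivers the intervention, so the verification is neither blinded nor independent.

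Any difference in capture between arms goes straight into the odds ratio from the logistic regression. If true control linkages are missed more often, the estimate favours the intervention. The results are meant to inform a future multilevel trial, so a distorted linkage difference would be carried forward.

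**Working it through.** **1. The two rules side by side**

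| Source | Text | Table 1 | Available to controls as described |
|---|---|---|---|
| Self-report | not named | named | yes |
| Navigator | named | not named | no navigator described |
| Provider collateral, if agreed | named | named | yes, if agreed |

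The missing navigator in the table does not look like shorthand. Table 1 lists navigator report for three secondary outcomes: the PrEP continuum, the substance use treatment continuum and linkage to other services. For this primary outcome it does not.

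**2. What each reading implies**

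- *Text alone:* navigator or collateral in one arm, collateral only in the other. Ascertainment differs by arm.
- *Both combined (self-report, then checked by navigator and provider):* the navigator check exists in one arm only. Ascertainment still differs.
- *Table 1 alone:* the same named sources in both arms. No asymmetry arises from the navigator.

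**3. Illustration of size under the text rule**

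The document states no linkage rate, capture rate, alpha or power, so there is no figure of its own to reproduce beyond the allocation: 75 × 2/3 = 50 and 75 × 1/3 = 25, which is consistent.

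Assumptions (not from the document): the same true linkage p in both arms, so no true effect; every intervention-arm linkage captured; a fraction s of control linkages captured.

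- Observed rates: intervention p, control p × s.
- Apparent odds ratio: [p/(1 − p)] ÷ [ps/(1 − ps)].
- Rejection rate: exact enumeration over Binomial(50, p) and Binomial(25, ps), two-sided likelihood-ratio test at nominal 5%.

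| p | s | Observed rates | Odds ratio | Rejects |
|---|---|---|---|---|
| 20% | 1.00 | 20% vs 20% | 1.00 | 5.4% |
| 20% | 0.90 | 20% vs 18% | 1.14 | 6.0% |
| 20% | 0.75 | 20% vs 15% | 1.42 | 9.0% |
| 20% | 0.50 | 20% vs 10% | 2.25 | 21.9% |
| 40% | 1.00 | 40% vs 40% | 1.00 | 5.6% |
| 40% | 0.90 | 40% vs 36% | 1.19 | 6.8% |
| 40% | 0.75 | 40% vs 30% | 1.56 | 14.1% |
| 40% | 0.50 | 40% vs 20% | 2.67 | 44.1% |

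Worked line: for p = 0.40 and s = 0.50 the control rate is 0.40 × 0.50 = 0.20, and the odds ratio is (0.40/0.60) ÷ (0.20/0.80) = 0.667 ÷ 0.25 = 2.67.

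**4. A second set of assumptions**

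With 95% capture in the intervention arm, 80% down to 50% in controls, true linkage of 20% to 50% and a pooled chi-square test, the apparent odds ratio runs from 1.23 to 2.71 and the rejection rate from 5.8% to 49.1%. With equal capture of 90% in both arms the odds ratio is 1.00 and the rejection rate is 5.1% to 5.9%.

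**The case against.** The strongest reply is that Table 1 is introduced as giving further detail on the outcomes, so the two statements could be complementary: self-report as the source, with navigator and provider as checks. Table 1's own rule treats both arms alike. This limits the point. A reader might infer that linkage is certain to be counted differently in the two arms, or that some measurement difference follows whichever rule is used. The document does not support either inference, because under Table 1 alone the navigator plays no part. But the complementary reading does not remove the problem, since it puts the navigator check back in one arm only.

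Three other inferences also go beyond the document.

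- That agreement to collateral is chosen after randomisation: the timing for aim 3 is not given. Consent and baseline come before randomisation; release forms appear only in the sample content of navigator session 1.
- That controls definitely have no navigator: this is a sound inference from the Standard of Care section, but it is not stated outright, and the flow figures are not available here.
- That no objective source exists for controls: Table 1 lists the medical record, without restriction by arm, for the secondary substance use treatment continuum. It is not named for the primary outcome.

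The illustration depends on the assumed rates. At 90% control capture the rejection rate stays close to nominal. This is also a pilot of feasibility, acceptability and preliminary impact with no stated alpha, so the shift in the odds ratio matters at least as much as the rejection rate.

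**Conclusion.** The point holds in this form: one of the two primary outcomes has two incompatible source rules, and the one in the text cannot be applied equally to both arms as they are described. The defect lies in what the article states, not in something left to an analysis plan. An analysis plan also cannot supply a verifier to an arm that has none once data collection has started.

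Whether bias arises depends on which rule is followed. The text rule, or a combination, builds differential ascertainment into the primary comparison; Table 1 alone does not, apart from collateral depending on agreement. The size cannot be derived from the document. In the illustration, with no true effect and full intervention-arm capture, it ranges from negligible (rejection of 6-7% at 90% control capture) to serious (22-44% at 50%, with apparent odds ratios of 2.25 to 2.67).

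**What to change.** Before aim 3 opens:

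1. Reconcile the text and Table 1 to one source rule applied identically in both arms. The Table 1 rule would serve: self-reported attendance, with date, at the 1-month and 3-month assessments, in the interview or web mode already planned.
2. Seek provider or record confirmation in the same way in both arms, and ask every participant for permission at consent, before randomisation.
3. Remove the navigator as a verifying source for this primary outcome. Keep navigator tracking as descriptive data on delivery.
4. Report provider-confirmed linkage as a sensitivity analysis, with the number agreeing to collateral by arm.

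The cost is small: a revised outcome sentence, a matching Table 1 entry and a permission item at consent. The downside is that self-report is unblinded and less certain than verified attendance. If over-reporting were commoner in the intervention arm, it would favour the intervention. The sensitivity analysis only partly addresses this, because it depends on agreement to collateral.
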